### 2.24. Data Analysis

#### Describing the Data

Our final data set will be at an individual patient level. Continuous data (e.g., age, length of stay) will initially be described using means and standard deviations. Categorical variables (e.g., gender) will be reported as numbers and proportions. We will use tables to summarise the characteristics of study participants (nurses and patients).

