### 2.12. Nurse-Level Data

#### Roster Data

Roster data will be extracted from CHRIS21 and Kronos for the time period 6 January 2020 through 5 March 2020. System Performance Support [21] defined a roster as a timetable that specifies the number of nurses and their classifications required for each shift. Data on the training nurses have received will be extracted and coded: 1. Mental health nurse, 2. Comprehensive nurse, 3. Enrolled nurse, 4. Nursing assistant, 5. Student nurse. Nurse unit managers will be asked to extract and code data from the shift roster about whether nurses have mental health nursing qualifications. We estimate that data extraction and coding should take no more than four hours of a nurse unit manager’s (NUMs) time. We will check with NUMs during the conduct of the study if the tasks were overly burdensome. We defined a mental health nurse as a registered nurse with a formal educational qualification in mental health nursing. A comprehensive nurse is a registered nurse with a formal educational qualification in general/comprehensive nursing and does not hold a formal mental health nursing qualification. An enrolled nurse is a nurse with a certificate or diploma qualification in nursing and is registered as an enrolled nurse. First level nurse refers to mental health and comprehensive nurses. Second level nurses are enrolled nurses. These data will be entered onto a data extraction form available as Supplementary Document (Table S3).

We will use the total number of nurses working each day as the denominator and then calculate the ratio of 1. Mental health nurse to comprehensive nurse, 2. Registered nurse to enrolled nurse, 3. Qualified nurse to unqualified staff.

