### 2.14. Data Storage

Data from participating hospitals will be transferred to the participating University in Victoria through the Cloudstor file transfer. CloudStor is a secure online service that was developed by Australia’s Academic and Research Network (AARNet) that enables universities and the wider community to quickly and securely synchronise, share and store files using the high-speed AARNet network. Data will be stored on a password protected CloudStor and only the researchers will have access. Patient and nurse data will be stored in separate files and then combined to enable analysis.

Following completion of the study, all data collected will be stored by the participating University for seven years following the Public Records Act 1973. We do not intend to make these data available to other researchers because this is a feasibility study, and we do not intend to undertake any formal tests of association.

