### 2.23. Management of Missing Data

We will determine if there is a pattern to missing values, are data missing at random or is there a systematic reason for the missingness of data, i.e., missingness depends at least in part on unobserved variables [26].

We will use Little’s MCAR test to assess if data are missing completely at random (MCAR). The data will be assumed to be MCAR if the *p*-value for Little’s MCAR test is not significant. If data are not MCAR, we will conduct further exploratory tests to determine missingness at random (for example, the significance tests of missingness). The significance tests of missingness will determine if data are missing at random (MAR) or missing not at random (MNAR) [26].

The key variables in this study are readmission and the educational preparation of nurses. A listwise deletion method will be used where data are missing completely at random, and the missing data include either of the two key variables. The use of listwise deletion, in this case, is appropriate because data for patients with no outcomes and data for nurses missing educational preparation cannot be analysed to give the association between patient outcomes and educational preparation of nurses.

We will use the pairwise deletion method where data will be missing completely at random and do not involve key variables (i.e., readmission). This will enable us to retain data and minimise the potential for selection bias.

If data are MAR, multiple imputations will be used using three steps: Imputation, completed-data analysis (estimation), and pooling step [27]. We will use listwise deletion if data are MNAR since there is no acceptable remedy for it [26].

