### 2.25. Calculating Nursing Skill Mix

Each patient will have an individual row in the dataset. For each day (07:00 to 06:59) that the patient is in hospital, we will calculate the total number of registered nurses, unqualified nurses, mental health nurses, comprehensive nurses, enrolled nurses, student nurses, nursing assistants, and total number of patients on the ward. We will use these data to compute the following skill mix ratios on a day-by-day basis:○Mental health nurse to comprehensive nurse.○Qualified nurse to nursing assistant.○All nurse (including nursing assistant) to patient.○Mental health nurse to patient.○Comprehensive nurse to patient.

To compute the final skill mix measure, we will calculate averages for the duration of their admission, using days of admission as the denominator. For example, to calculate the comprehensive nurse to mental health nurse ratio. we would perform the following calculation. A patient was in hospital for three days. On the first day, there were eight comprehensive and two mental health nurses who provided care. On the second and third days, respectively, there were nine and ten comprehensive and three and four mental health nurses. This would give us a skill mix ratio of comprehensive to mental health nurses of 3:1.

To calculate nursing hours per patient day, we will total the number of nurses working on a given day, multiply by seven days and then divide by the number of patients on the ward at midnight.

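### Staffing is a ward-day measure, but the only final file described has one row per patient; stays running past 5 March 2020 include days without staffing data, which the averaging divisor ignores

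*Protocol article*

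**What the plan says.** In the protocol article, section 2.24 sets the unit of the final file: "Our final data set will be at an individual patient level". Section 2.25 repeats it: "Each patient will have an individual row in the dataset".

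Staffing is counted by day. The Roster Data text under section 2.12 says "We will use the total number of nurses working each day as the denominator", and section 2.25 says "We will use these data to compute the following skill mix ratios on a day-by-day basis". These daily values reach the patient row as a stay average: "we will calculate averages for the duration of their admission, using days of admission as the denominator".

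Roster data (section 2.12) and the daily inpatient count (section 2.10) are both extracted for 6 January to 5 March 2020 and for no later date. Section 2.3 ties eligibility to an inpatient admission in that window and sets no latest discharge date.

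On missing values, section 2.23 names readmission and nurse education as the key variables and says: "A listwise deletion method will be used where data are missing completely at random, and the missing data include either of the two key variables". Listwise deletion also applies if data are judged missing not at random; multiple imputation applies if they are missing at random. The Limitations add that agency nurses' education is not recorded.

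Section 2.14 gives the file handling before linkage: "Patient and nurse data will be stored in separate files and then combined to enable analysis".

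**The concern.** All patients on a ward on the same day share one set of nurse counts and one census, so the unit of staffing information is the ward-day. Three things follow if it is described and cleaned only on patient rows.

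- **Description.** A mean and SD of skill mix over patients weights days by occupancy, and its spread depends on length of stay. It does not give the between-ward and within-ward variation that a powered study would need as a design input.
- **Coverage.** A stay that continues after 5 March 2020 has days for which no roster or census is extracted, yet the stated divisor is the whole stay.
- **Completeness.** The aim is to show that these data can be extracted and linked. Completeness counted on patients instead of ward-days could look much worse than it is, and deleting on that basis would fall most on long stays.

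**Working it through.** **1. Window.** 6 January to 5 March 2020 inclusive is 26 + 29 + 5 = 60 days, which reproduces the figure in section 2.10. Section 2.10 of the article and its setting section (2.1) give one rural unit and two metropolitan wards. If the latter are rostered separately, there are 3 × 60 = 180 ward-days, of which 60 are rural and 120 metropolitan.

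**2. Weighting on patient rows.** Let patient *i* stay *Lᵢ* days and let *r_d* be the ratio on ward-day *d*. The mean over *N* patients of their stay averages is (1/N) Σᵢ (1/Lᵢ) Σ_d r_d. Ward-day *d* therefore has weight (1/N) × the sum of 1/Lᵢ over the patients present that day. With equal stays this is proportional to the number present, so one day on the full six-bed rural unit enters six averages.

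The spread changes too. If daily ratios varied independently with SD *s* (an assumption), a stay average would have SD s/√L: 0.58*s* for 3 days, 0.38*s* for 7 and 0.27*s* for 14. Positive correlation between days makes the shrinkage smaller. The SD over rows thus mixes staffing variation with length of stay.

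**3. Days without staffing data by design.** Assume admissions spread evenly over the 60 days, a fixed stay of *L* days and no discharge cut-off. A stay runs past day 60 if it starts on one of the last L − 1 days, so the share is (L − 1)/60:
- L = 7: 6/60 = 10%
- L = 14: 13/60 = 22%

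The article gives no length of stay; both values are assumed.

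**4. Effect of the divisor.** Section 2.25's example has comprehensive nurses 8, 9, 10 and mental health nurses 2, 3, 4. The totals give 27/9 = 3, which reproduces its 3:1. The mean of the daily ratios is (4 + 3 + 2.5)/3 = 3.17. Now suppose day three has no data:
- Mean of daily ratios over days of admission: (4 + 3)/3 = 2.33.
- Mean of daily ratios over days with data: (4 + 3)/2 = 3.50. The first figure is one third lower.
- Ratio of totals: (17/3)/(5/3) = 17/5 = 3.40, whatever the divisor.

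In general, an average of daily ratios falls short of the covered-day average by the fraction (uncovered days)/(days stayed). A 10-day stay from 3 March has three covered days, so the shortfall is 7/10 = 70%.

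**5. If listwise deletion were applied to patient rows.** The text leaves this open, so the figures are conditional. With *k* of a ward's 60 days lost at random, a stay of *L* days inside the window is hit with probability 1 − C(60 − L, k)/C(60, k):

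| Ward-days lost | L = 3 | L = 7 | L = 14 | L = 30 |
|---|---|---|---|---|
| 1 of 60 (1.7%) | 5% | 12% | 23% | 50% |
| 6 of 60 (10%) | 28% | 54% | 81% | 99% |

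Both *k* and *L* are illustrative. The pattern holds for any values: patient-level loss exceeds ward-day loss for any stay longer than a day, and it rises with length of stay.

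**The case against.** The strongest reply has five parts.

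- **The daily data already exist.** Nurse data are first held in their own file, ratios are computed daily, and tables are planned for nurses as well as patients. This stands: a ward-day summary is possible. None is specified, though, and the only final file described is the patient file.
- **The exposure suits the aim, and nothing is tested.** A stay average per patient is a sensible exposure for readmission, and section 2.26 rules out inference. Both stand. A reader might infer that shared ward-days distort standard errors or p-values; none is planned, so they cannot. The point concerns description, completeness and design inputs.
- **The deletion rule may not reach patients.** Section 2.23 can be read as dropping a patient without an outcome and a nurse record without an education code. That is a fair reading, and nowhere is a patient said to be dropped for one lost roster day. Step 5 is therefore a risk to close off, not a stated error. The one gap the article names, agency nurses' education, is per nurse, and no rate of lost roster days is given.
- **The divisor cancels in the worked example.** True for a ratio of totals. The preceding text describes day-by-day ratios that are then averaged, and there it does not cancel.
- **The uncovered tail may be unintended.** Section 2.11 ends the patient study period on 5 March 2021, and 12 months of follow-up fit within that only for discharges by 5 March 2020. If that were an eligibility rule, the tail would vanish. Section 2.3 does not make it one.

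**Conclusion.** The point holds as a matter of method and reporting, of moderate weight. Staffing is a ward-day quantity, the described final file is by patient, and the stated divisor takes no account of days without staffing data. Under even admissions and no discharge cut-off, about 10% of 7-day and 22% of 14-day stays would have such days. The understatement per affected stay equals the uncovered fraction, and it arises only where daily ratios are averaged.

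Two stronger readings are tempting and are not supported:
- **That one lost roster day touches about a quarter of patients.** This needs a stay of roughly 14 to 20 days, which the article does not give, and it applies to the patients of one ward only. For stays of 7 to 30 days the share of that ward's patients runs from about 11% to 50%, depending also on whether everyone present or only those admitted in the window is counted.
- **That pooled figures mostly describe the larger site.** The article does not say that figures are pooled across sites and gives no metropolitan bed number. With equal stay and occupancy, metropolitan patients outnumber rural ones once those two wards together exceed six beds. That makes the direction likely, but it is not a rule or figure in the plan.

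**What to change.** 1. Before linkage, keep the daily counts as a ward-day file: ward code, date, nurse counts by category, and census. This is 180 rows if the two metropolitan wards are rostered separately.
2. On that file, report by ward the number of missing ward-days and the distribution of each ratio (median, quartiles, range).
3. Link to patient stays and average over days with staffing data instead of all days of admission.
4. Carry days covered divided by days stayed on each patient row, so that stays running past 5 March 2020 are visible.
5. State in section 2.23 that a missing ward-day does not delete a patient, and to which unit (nurse record, ward-day or patient) each missing-data rule applies.

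The stay average stays in place as the exposure. The cost is one file, one extra table and a few sentences, since the daily counts are already to be calculated.

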### 2.25. Calculating Nursing Skill Mix

Each patient will have an individual row in the dataset. For each day (07:00 to 06:59) that the patient is in hospital, we will calculate the total number of registered nurses, unqualified nurses, mental health nurses, comprehensive nurses, enrolled nurses, student nurses, nursing assistants, and total number of patients on the ward. We will use these data to compute the following skill mix ratios on a day-by-day basis:○Mental health nurse to comprehensive nurse.○Qualified nurse to nursing assistant.○All nurse (including nursing assistant) to patient.○Mental health nurse to patient.○Comprehensive nurse to patient.

To compute the final skill mix measure, we will calculate averages for the duration of their admission, using days of admission as the denominator. For example, to calculate the comprehensive nurse to mental health nurse ratio. we would perform the following calculation. A patient was in hospital for three days. On the first day, there were eight comprehensive and two mental health nurses who provided care. On the second and third days, respectively, there were nine and ten comprehensive and three and four mental health nurses. This would give us a skill mix ratio of comprehensive to mental health nurses of 3:1.

To calculate nursing hours per patient day, we will total the number of nurses working on a given day, multiply by seven days and then divide by the number of patients on the ward at midnight.

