### 2.9. Kronos

Kronos is a suite of workforce management tools [19]. Employee demographic information, hours worked, and periods of leave are all recorded in the system [19].

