### 2.10. Patient-Level Data

From the relevant electronic patient records, we will extract and code (details of how we will code in parentheses) the following variables: Age (age in years at point of hospital admission), gender (coded: 1. Male, 2. Female, 3. Other), employment status at the point of admission (coded: 1. Employed, 2. Unemployed, 3. Student, 4. Retired, 5. Other), primary psychiatric diagnosis (coded: 1. Mood and/or anxiety disorder [including bipolar], 2. Schizophrenia, 3. Personality disorders, 4. Other [specify]), psychiatric comorbidities (coded: 1. Yes, 2. No), substance use (coded: 1. Yes, 2. No), physical comorbidities (coded: 1. Yes, 2. No), date of admission (dd/mm/20yy), detained under mental health law (coded: 1. Yes, 2. No), on a Community Treatment Order prior to admission to hospital (coded: 1. Yes, 2. No), when was the patient discharged from the participating ward? (dd/mm/20yy), Discharged on a Community Treatment Order (coded: 1. Yes, 2. No), admitted by inpatient psychiatric services at the participating hospitals within 12 months of discharge (coded: 1. Yes, 2. No), number of psychiatric admissions during the study period, Health of the National Outcome Scales (HoNOS) total score on admission to hospital, HoNOS total score immediately prior to discharge (recorded as number). Health of the Nation Outcome Scales (HoNOS) is a clinician rated tool comprising 12 simple scales assessing behaviour, impairment, symptoms and social functioning for those in the 18–64 years old age group [20]. We will request the unit managers to extract information on the total number of inpatients on the ward at morning handover (07:00 am) each day between the 6 January 2020 and 5 March 2020 (60 days). The patient data extraction form is available as Supplementary Document (Table S2).

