### Limitations

We have not tested the validity and reliability of routine hospital data collection, which is common in this type of research. Routinely collected health data in research studies are accepted as valid and reliable in Australia and worldwide. For example, in the United Kingdom, routine primary care data have been used in research for almost 30 years [28]. Still, the accuracy of the data has never been checked. Hospitals do not collect data on agency nurses’ educational preparation, which may affect the precision of our skill mix estimates. Nursing hours per patient day estimate the total amount of care time available. Likely, it is an overestimate of the actual amount of bedside nursing care patients receive.

We proposed extracting nurse data on gender, age, years of experience, and the type of contract (full-time or part-time), however, the human research ethics committee advised that these data were not required to achieve the aims of the study. It may be important to collect these data in future studies where it will be necessary to adjust for confounding in any proposed analysis. COVID-19-related data, such as isolation, vaccination status, or infections, which could be confounding factors, will not be retrieved. We anticipate that data on COVID-19 would be difficult to obtain.

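### The formula for nursing hours per patient day contains no hours, and its midnight divisor does not match the 07:00 census that the study requests

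*Protocol article*

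**What the plan says.** Section 2.25 (Calculating Nursing Skill Mix) gives the rule in one sentence. The numerator starts from a head count: "we will total the number of nurses working on a given day". The analyst is then to "multiply by seven days and then divide by the number of patients on the ward at midnight".

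Four other places bear on it:

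- Section 2.25 itself sets the day used for staffing counts: "For each day (07:00 to 06:59) that the patient is in hospital".
- Section 2.10 (Patient-Level Data) asks unit managers for the "total number of inpatients on the ward at morning handover (07:00 am) each day". This is the only ward census that the article requests.
- Section 2.12 (Roster Data) describes what is taken for nurses. It covers roster data and training category: "Data on the training nurses have received will be extracted and coded". Hours and shift length are not listed. Section 2.9 says of Kronos, the Victorian system: "Employee demographic information, hours worked, and periods of leave are all recorded in the system". Section 2.8 describes Chris21, the South Australian system, only as software into which timesheets can be entered.
- The Limitations say how the measure is to be read: "Nursing hours per patient day estimate the total amount of care time available".

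**The concern.** A measure of nursing hours per patient day needs hours of nursing in the numerator and patients for the same day in the denominator. The stated rule has neither a shift length nor recorded hours. It scales one day's head count by seven days and sets it against one day's patient count. What comes out is not care time, although the Limitations interpret it as care time.

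The divisor adds a second problem. Midnight appears nowhere else in the article. The census that managers are asked for is at 07:00, and the staffing day starts at 07:00. An analyst holding the 07:00 count must either depart from the formula or build a midnight count by a method that the article does not describe.

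The study exists to show whether staffing measures can be calculated from administrative data at two sites with different systems. A formula that each site could resolve differently weakens that demonstration for this measure.

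**Working it through.** The article gives no numerical value for nursing hours per patient day, so there is no figure to reproduce. The check is one of units, followed by an illustration.

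**Units**

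- Rule as written: nurses × 7 days ÷ patients = nurse-days per patient.
- Rule needed: total nursing hours in the day ÷ patients that day = hours per patient day.

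**When the two agree**

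Let N be nurses on the day, P the census and L the mean shift length in hours. The printed rule gives 7N/P and hours per patient day is LN/P. The ratio is 7/L, so the relative error is 7/L − 1, whatever the staffing or census. It is zero only if L = 7.

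**Illustration**

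Inputs from the article: the worked example in section 2.25 has 8 + 2, 9 + 3 and 10 + 4 nurses on three days, that is 10, 12 and 14. Section 2.1 gives the South Australian unit six beds. Assumptions: a census of 6 (the article does not tie its example to that unit) and the shift lengths in the table.

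| Rule | 10 nurses | 12 nurses | 14 nurses | Printed rule relative to this row |
|---|---|---|---|---|
| As printed, 7N/6 | 11.67 | 14.00 | 16.33 | – |
| Hours, L = 7 | 11.67 | 14.00 | 16.33 | 7/7 − 1 = 0% |
| Hours, L = 7.5 | 12.50 | 15.00 | 17.50 | 7/7.5 − 1 = −6.7% |
| Hours, L = 8 | 13.33 | 16.00 | 18.67 | 7/8 − 1 = −12.5% |
| Hours, L = 10 | 16.67 | 20.00 | 23.33 | 7/10 − 1 = −30% |

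The last column follows entirely from the assumed L.

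**Census time**

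The result is proportional to 1/P. On the six-bed unit, suppose the midnight and 07:00 counts differ by one patient (assumed):

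- dividing by 5 in place of 6: 6/5 − 1 = +20%
- dividing by 6 in place of 5: 5/6 − 1 = −16.7%

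The article does not say how often, or by how much, the two counts differ.

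**The case against.** The best defence is that days is a slip for hours. The measure's name and the Limitations both point to care time, and nurses times seven hours divided by patients has the right unit. On that reading the sentence is an ordinary constant-shift approximation, and preferring recorded hours is a matter of design. This is plausible, but it is a guess. It still requires the sentence to change, it applies one unstated length to morning, afternoon and night shifts, and it leaves the midnight conflict untouched.

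Several stronger readings are tempting and are not supported:

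- *That the measure will be wrong by a known percentage.* No shift length is given, so no true value can be derived. With 7-hour shifts the number would be correct.
- *That a midnight count is impossible.* Admission and discharge dates are extracted and could yield an approximate one. It would cover only included patients (aged 18 or older, stay of at least 24 hours), and the article does not propose it. The extraction forms (Tables S2 and S3) are not shown. What can be said is that two census times are named and must be reconciled.
- *That the numerator counts staff required, not staff present.* Section 2.12 cites a definition of a roster as "a timetable that specifies the number of nurses and their classifications required for each shift". That is a general definition. The formula itself, the nurse inclusion criteria and the rest of section 2.12 speak of nurses working, so this is not a defect of the formula.
- *That both systems readily supply hours worked.* Only Kronos is described as recording them. Both sites also use paper rosters, and the article does not say whether agency staff appear in either system.
- *That the error will pass into the powered study.* This is conjecture.

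**Conclusion.** The formula is wrong as written in two respects: it has no hours term, and its divisor is taken at a different time from the census requested and from the start of the defined day. Both follow from the text without assumption.

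The numerical consequence does rest on assumptions. It runs from 0% with 7-hour shifts to −12.5% with 8-hour shifts, and further if shifts are longer. A one-patient difference in the divisor would add about 17 to 20% in either direction on the six-bed unit.

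The measure is descriptive. It is not one of the five ratios listed in section 2.25, it is not one of the key variables named in section 2.23 (readmission and nurses' educational preparation), and section 2.26 rules out inference. This is therefore a should-fix correction. It does not put the study's main aim in doubt.

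**What to change.** Replace the sentence in section 2.25 with a definition of this form:

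> Nursing hours per patient day are the total nursing hours on the ward from 07:00 to 06:59, divided by the number of inpatients at the 07:00 census of that day.

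The multiplication by seven days and the reference to midnight are both deleted. The text should then state:

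- **Source of hours.** Use recorded hours worked where the system supplies them (Kronos; Chris21 timesheets if they can be retrieved). Otherwise use the head count on each shift times the stated length of that shift.
- **One method at both sites.** If recorded hours cannot be had at one site, use the head count with stated shift lengths at both.
- **Agency staff.** Say how they are counted.

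The cost is small: a change of wording, plus either one extra field from systems already in use or an explicit shift-length assumption. An extra nurse field may need to go back to the ethics committee, since the Limitations report that it advised against other nurse variables. The shift-length route avoids that. The 07:00 census is already being requested, so the divisor needs no new data.
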